### Scientific research questions

What are the effects of a school-based programme including physical activity and homework support during an extended school day on mental and physical health, physical activity, cognitive function, and academic performance?Are there any differences in the effects of the intervention in relation to gender, socioeconomic status, and neurodevelopmental conditions (e.g. ADHD, autism)?How is the programme implemented with regard to fidelity, dose, feasibility, acceptability, and context? What are the barriers and facilitators identified in the implementation of the intervention?

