Cognitive function will be assessed using a computer-based test battery measuring working memory (letter updating), episodic memory (word recall), and perceptual speed (number comparison). Using three different domains of cognitive function and multiple trials allows for a broader understanding of cognitive function and increases the reliability of the test while keeping participant burden to a minimum. This design also allows for the construction of a latent variable for cognitive function. A previous study has shown a version of this test battery to be a valid and robust measure of these cognitive abilities in an older population [42].

Academic performance in Swedish, English, and mathematics will be measured by grades and standardised Swedish national tests collected from the Statistics Sweden (SCB) register (grade 9) and directly from the schools (grades 7 and 8).

Body mass (kg) and height (cm) will be measured in duplicates using standardised procedures with SECA instruments. Body Mass Index (BMI) will be calculated as body mass (kg) divided by height (m) squared. Overweight and obesity will be defined according to the International Obesity Task Force standard deviation score (BMI sds), computed according to a Swedish reference standard [43].

Health behaviours will self-reported in a questionnaire. Physical activity and sedentary behaviours include questions about transport to and from school, physical education attendance, participation in organised sports/activities, and screen time use. Dietary intake will be assessed by self-report in a questionnaire, based on a composite score of indicator foods, including healthy foods (fruit and vegetables), unhealthy foods (sweets and ice cream), and sugar-sweetened beverages.

Sleep will be measured and expressed as total sleep time and efficiency using a questionnaire where the participants report when they usually go to bed and wake up.

Motivation to physical activity will be measured using an adapted version of the Behavioural Regulation In Exercise Questionnaire (BREQ) [32].

Functional disabilities will be self-reported using the Modified Child Functioning Module [44].

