Background characteristics: Parental educational level will be collected from the SCB register as an indicator of socioeconomic status. The highest level of education attained in the household will be used and dichotomised into low education (≤ 12 years) and high education (> 12 years). Parental country of birth will be self-reported in a questionnaire. Information about school type (independent or public) will be collected from the National Agency for Education.

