**Parents**

Information about family background, lifestyle, the child’s physical activity, health, and possible medical diagnoses or disabilities, including neurodevelopmental disorders, will be self-reported by parents in questionnaires.

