### Sample size calculation

To obtain an effect size of intervention Cohen’s d = 0.35 in anxiety (based on a meta-analysis [18]) in a population with the average correlation between cluster of 0.02, a variance of 5 points in the primary outcome SCAS-S, a two-tailed significance test (α = 0.05), and a power of 80%, it is required to include at least 27 schools in the intervention group and 27 schools in the control group with 50 students from each school. Anxiety will be assessed with the questionnaire Spence Children’s Anxiety Scale Short Version (SCAS-S) [34].

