### Data analysis

Baseline differences in continuous demographic variables between the intervention and control groups will be presented using means and standard deviations (SD) for normally distributed data and compared using independent t-tests. For non-normally distributed data, medians and ranges will be reported, with analyses conducted using non-parametric tests. Categorical variables will be described as proportions, and group differences will be examined using chi-square tests. The effects of the intervention on primary and secondary outcomes will be analysed through mixed-effects regression models with two hierarchical levels (individual and school), using post-intervention data and following the intention-to-treat approach. Initially, a crude model will be tested for each outcome at post-intervention, including group allocation as a predictor and adjusting for baseline values of the corresponding outcome. In a second model, gender and parental education will be added to the model. Interactions between group and gender, or group and parental education, will be tested and, if significant, analysed using stratified models All participants with baseline measurements will be included, and missing data will be addressed using multiple imputation The potential impact of missing data on the results will be evaluated through sensitivity analyses. Additionally, the analysis will be performed per protocol, including only those participants with high fidelity to the intervention components. All analyses will be performed blinded to group allocation. The data analysis plan was submitted as part of the trial registration (ISRCTN78666212).

All focus groups and interviews will be audio-recorded, transcribed verbatim, and analysed using qualitative analysis, including content [50–52]- and thematic analysis [53, 54]. The documented data on dose and fidelity will be analysed with descriptive statistics.

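### Research question 2 names three effect modifiers but the analysis section tests only two, and subgroup effects are planned only after a significant interaction

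*Protocol article*

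**What the plan says.** Under Scientific research questions, the second question reads: "Are there any differences in the effects of the intervention in relation to gender, socioeconomic status, and neurodevelopmental conditions (e.g. ADHD, autism". That is three modifiers.

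The Data analysis section describes a crude mixed model (individual and school levels) with allocation and the baseline value of the outcome. It continues: "In a second model, gender and parental education will be added to the model". On effect modification it says: "Interactions between group and gender, or group and parental education, will be tested and, if significant, analysed using stratified models".

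Parental education stands in for socioeconomic status: "Parental educational level will be collected from the SCB register as an indicator of socioeconomic status". The two planned interactions therefore match the first two modifiers in the question.

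The third modifier has a data source. In the parent questionnaire, "possible medical diagnoses or disabilities, including neurodevelopmental disorders, will be self-reported by parents in questionnaires". A related student measure is also collected: "Functional disabilities will be self-reported using the Modified Child Functioning Module". Neither appears in the Data analysis section as an interaction, a stratum or a covariate.

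The section also points to a further document that is not shown: "The data analysis plan was submitted as part of the trial registration (ISRCTN78666212").

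**The concern.** There are two separate points.

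1. **A modifier without an analysis.** The article lists its interaction tests by name, and the list is one short of its own research question. If no other document fills the gap, any later comparison by ADHD or autism would be post hoc, even though the question was posed in advance and the data were collected for it.

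2. **The gate on subgroup models.** Effects within boys and girls, or within low and high parental education, are planned only when the interaction test is significant. Estimates that appear only after passing a significance threshold overstate the difference on average, most of all when power is modest. When the test fails, no subgroup estimates are planned. The article's abstract and discussion expect a contribution to reducing inequalities. A reader judging that expectation needs the effect by socioeconomic group with its interval, whether or not p falls below 0.05.

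**Working it through.** **Side-by-side check (no arithmetic needed)**

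| Modifier in research question 2 | Data source | Interaction in Data analysis |
|---|---|---|
| Gender | student data | yes |
| Socioeconomic status | parental education, SCB register | yes |
| Neurodevelopmental conditions | parent questionnaire | none named |

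Three asked, two tested, one without an analysis.

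**How much the gate can matter (illustration)**

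The article gives no power figure for any interaction, so there is no stated number to reproduce.

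Inputs from Sample size calculation: 27 schools per arm × 50 students = 1,350 per arm, ICC 0.02, two-sided α 0.05. Assumptions: a modifier that varies between students within schools, with the same prevalence p in both arms; no loss; no baseline adjustment; outcome in SD units. The prevalences of neurodevelopmental conditions (10% and 5%) are assumed, because the article gives none.

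The interaction contrast compares students within schools, so the between-school variance drops out and each cell contributes residual variance 1 − 0.02 = 0.98:

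SE = √{2 × 0.98 × [1/(1350p) + 1/(1350(1 − p))]}

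80% power is reached at (1.96 + 0.84) × SE = 2.80 × SE, and 50% power at 1.96 × SE.

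| p | SE | 80% power at | 50% power at |
|---|---|---|---|
| 0.50 (e.g. gender) | 0.076 | 0.21 SD | 0.15 SD |
| 0.10 | 0.127 | 0.36 SD | 0.25 SD |
| 0.05 | 0.175 | 0.49 SD | 0.34 SD |

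The last two rows show what an added neurodevelopmental test could detect. They say nothing about the present gate, because no such test is planned.

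**Selection after significance, 50/50 modifier**

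Power = Φ(δ/SE − 1.96). The mean estimate among results significant in the true direction is δ + SE × φ(1.96 − δ/SE)/power.

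- True interaction 0.175 SD (half of 0.35, for illustration): δ/SE = 2.296; power 63%. Mean significant estimate = 0.175 + 0.0762 × 0.377/0.632 ≈ 0.22 SD, which is 26% too large.
- True interaction 0.10 SD: δ/SE = 1.312; power 26%. Mean significant estimate = 0.10 + 0.0762 × 0.323/0.259 ≈ 0.195 SD, nearly double.

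In the first case the stratified models would not be run about 37% of the time; in the second, about 74%.

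**Direction of the simplifications**

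The planned baseline adjustment improves precision by a factor √(1 − r²). With an assumed baseline correlation r of 0.6 the factor is 0.8, and the 80%-power figures become about 0.17, 0.28 and 0.39 SD. Attrition and parent non-response work the other way. Parental education probably clusters by school, so the formula fits it less well than gender and no figure is given for it.

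**The case against.** The strongest reply is that the article is a condensed document and refers to an analysis plan lodged with the registration. That plan may contain a neurodevelopmental analysis and will probably say which tables are reported. Testing the interaction first and stratifying only if it is significant is also a common safeguard against over-reading subgroups, and it makes the plan neither contradictory nor unworkable.

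Much of this stands, and it limits the point. Three stronger readings are tempting but unsupported:

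- **That non-significant interactions would be suppressed.** The interactions are to be tested without condition; only the stratified models are gated. Nothing says that interaction estimates or their intervals will be withheld.
- **That any difference below the 80%-power figures would usually fail the gate.** A test fails more often than it passes only below 50% power, about 0.15 SD for a 50/50 modifier. At 0.175 SD it still passes 63% of the time.
- **That the trial cannot answer its question on ADHD and autism.** The data are collected. What can be said is that this article specifies no analysis for them.

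What does not stand is the appeal to the unseen plan as a complete answer. Silence on subgroups would be normal in an article. An explicit list that omits a modifier named in the article's own research question is a mismatch between two of its sections, and it needs reconciling whatever the registered plan says.

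**Conclusion.** The mismatch is established from the text alone and rests on no assumption: neurodevelopmental condition is in research question 2 and absent from the stated analysis.

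The criticism of the gate is a recommendation for better practice, not an error in the plan. Its size is moderate. For a 50/50 modifier, true interactions between about 0.15 and 0.21 SD have 50% to 80% power, so subgroup models would often be skipped, and when they are run the difference would be overstated (by roughly a quarter at 0.175 SD). These figures assume full recruitment, ICC 0.02, no loss and no baseline adjustment.

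The main-effect analysis of the primary outcome is unaffected. The point should be addressed, but it does not threaten the trial's main conclusion.

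**What to change.** 1. Reconcile Scientific research questions with Data analysis. Either add a group × neurodevelopmental condition interaction using the parent-reported data already collected, or remove neurodevelopmental conditions from research question 2. If the interaction is added, the trial team should state how the variable is coded and when the parent report is taken, since the article gives neither.
2. For all three modifiers (or the two that remain), report the interaction and the effect in each subgroup with 95% CIs from the single full-sample mixed model, whatever the p value. Use this in place of the significance-gated stratified models, which re-estimate school variance and covariates on part of the data.
3. Label these results exploratory.

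Cost: one extra model term, a few sentences of text and no new data collection. Precision for neurodevelopmental conditions will be modest (80% power at about 0.36 SD for 10% prevalence and 0.49 SD for 5%, both assumed) and will depend on how many parents return the questionnaire. The intervals will show this openly.

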#### Data collection

Data for the outcome measures will be collected before and after the intervention. Baseline data will be collected in the autumn of 2021 (first wave), autumn 2023 (second wave), and autumn 2024 (third wave). Post-intervention data will be collected in the spring of 2022 (first wave), spring of 2024 (second wave), and spring of 2025 (third wave). One-year follow-up measures will be collected in the spring of 2025 and 2026. Data for the process evaluation will be collected continuously during the intervention (observations and documentation) during the school years: 2021–2022, 2023–2024, and 2024–2025. All measurement methods and routines have been tested with adolescents in the school setting.

Students in both the intervention and control groups will receive a gift card worth 150 SEK (≈ 15 €) as compensation after each measurement. Additionally, participants in the intervention group will receive audiobook subscriptions during the intervention while those in the control group will receive the same after the follow-up measurements.

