#### Measurements

The measurements will be conducted by trained healthcare professionals and researchers who visit the schools and carry out the assessments before lunch on the test days. These measurements include questionnaires administered via a secure online survey tool, accelerometers to assess physical activity and sedentary time, height and weight measurements, and a cognitive test battery.

The parents, teachers or teachers’ assistants of physical activity sessions and headteachers also fill out online questionnaires. Reminders will be sent by e-mail and text messages up to three times.

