##### Secondary outcomes

**Students**

Mental health will be self-reported in questionnaires. Health-related quality of life will be measured with the questionnaire Kidscreen-10 [36], stress with the single item stress question (SISQ) [37], psychosomatic health problems with the Psychosomatic Problem Scale (PSP), and self-esteem with the Rosenberg Self-Esteem Scale (RSES) [38].

Physical activity and sedentary time will be measured with accelerometry, which is an objective way of assessing detailed physical activity patterns [39]. For seven consecutive days, physical activity patterns will be measured with triaxial accelerometers (model GT3X+, Actigraph, LCC, Pensacola, USA). Participants will be instructed to wear the accelerometer on their right hip during all hours when awake except during activities involving water. The accelerometers will be sent back to the researchers in pre-paid envelopes. The software ActiLife Data Analysis, will be used to process the accelerometer data. Uniaxial (vertical axis) data will be saved in 5-second epochs. Non-wear time will be defined as 60 min of 0 counts, with no spike tolerance. A filter will be applied to distinguish school-time physical activity from leisure-time activity, based on school schedules for each class. A valid day is defined as having at least 500 min of activity registration per day, and a minimum of 3 days, including at least one weekend day, will be considered a valid week. School time will be considered valid if there are at least two valid weekdays. Sleep time will be based on the self-reported questions. The physical activity outcomes will be time spent in sedentary, light physical activity (LIPA), and moderate to vigorous intensity (MVPA). The counts from the accelerometer data will be categorised into minutes spent in: sedentary intensity (0–100 counts/minute), LIPA (101–2295 counts/minute), and MVPA (≥ 2296 counts per minute) [40].School time will be determined using the start and end times of each school day, as extracted from the school schedules. The weekly average of ≥ 60 min of MVPA per day will be used to reach the physical activity recommendation, based on both school and leisure time. In sensitivity analyses, activity intensity will be divided into 25 categories for high resolution analysis. In these analyses, the innate low-pass filter at 1.63 Hz will be removed and replaced with a 4 Hz cut-off for better validity [41].

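### The main analysis claims intention to treat, but its only inclusion rule admits students by baseline measurement and so appears to leave out enrolled students who have an outcome and no baseline

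*Protocol article*

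**What the plan says.** All the rules on this point stand in the Data analysis section of the protocol article. The mixed models are fitted "using post-intervention data and following the intention-to-treat approach". The first model is described as "including group allocation as a predictor and adjusting for baseline values of the corresponding outcome". Who enters is then given in one sentence: "All participants with baseline measurements will be included, and missing data will be addressed using multiple imputation". Two further commitments follow: "The potential impact of missing data on the results will be evaluated through sensitivity analyses", with no content given, and a separate analysis, "Additionally, the analysis will be performed per protocol, including only those participants with high fidelity to the intervention components". No sentence brings in an enrolled student who has a post-intervention outcome but no baseline.

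The Measurements section explains how such students arise: staff "visit the schools and carry out the assessments before lunch on the test days". Under Data collection, baseline falls in autumn and the post-intervention measurement in the following spring. Under Intervention components, the programme is compulsory for every student in an intervention school, so a student absent in autumn is still exposed and can be measured in spring.

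**The concern.** Under intention to treat in a school-randomised trial, a student is analysed according to the school's allocation. Here entry depends on having been measured at one visit. If every enrolled student were analysed, the qualifier about baseline measurements would serve no purpose, so the rule and the claimed principle pull against each other within one paragraph.

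The rule also ranks information the wrong way round. A student with an observed outcome and a missing baseline has a missing covariate, and still informs the treatment comparison directly. A student with a baseline and a missing outcome adds essentially nothing to that comparison once the outcome has been imputed from the same covariates. The rule drops the first and keeps the second, although the planned imputation could handle both.

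Two things are at stake. One is some precision. The other is selection: the analysed set depends on attendance, which could plausibly be related to anxiety, the primary outcome. The documents do not establish that relation.

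**Working it through.** **Step 1. The plan's own figure.** The inputs, from Sample size calculation, are a difference of 0.35, variance 5, ICC 0.02, 50 students per school, two-sided α 0.05 and power 80%.

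- Design effect: 1 + (50 − 1) × 0.02 = 1.98.
- With 0.35 read as a difference in raw points and SD = √5, 641 students per arm are needed before clustering. Then 641 × 1.98 = 1,269, and 1,269 / 50 = 25.4 schools per arm. A t-based calculation on 52 degrees of freedom gives the stated 27, with power 81.0%.
- With 0.35 read as a true Cohen's d, 129 × 1.98 = 255 students, or 6 schools (7 t-based). The stated 27 is not reproduced. That mismatch is a separate matter.

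**Step 2. Students affected.** The documents give no absence rate, so the following are assumptions: 10% absent at baseline (15% as a second case), 90% of those with a baseline seen again, and 60 to 80% of baseline absentees present in spring. At 10% absence, per school of 50:

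- with a baseline: 45
- with baseline and outcome: 45 × 0.9 = 40.5
- with an outcome only: 5 × 0.6 to 5 × 0.8 = 3 to 4

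**Step 3. Variance without covariate adjustment.** The variance of an arm mean is proportional to 0.02 + 0.98/m.

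- Rule as written, m = 40.5: 0.02 + 0.98/40.5 = 0.0442.
- With outcome-only students, m = 43.5 to 44.5: 0.0425 to 0.0420.
- Ratio: 1.039 to 1.052.
- At 15% absence, m = 38.25 against 42.75 to 44.25: ratio 1.063 to 1.082.

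These are upper figures, because the planned model adjusts for baseline and a student without one gains less from that adjustment.

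**Step 4. Variance with baseline adjustment.** Assume a baseline-to-post correlation r of 0.6 to 0.7 and unchanged between-school variance. The within-school term becomes 0.98 × (1 − r²), and an outcome-only student counts as 1 − r² of a complete one: 0.64 at r = 0.6 and 0.51 at r = 0.7.

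| Case (10% absent) | Effective m | Variance, rule as written | Variance, all enrolled | Ratio |
|---|---|---|---|---|
| r = 0.7, 3 outcome-only | 40.5 + 3 × 0.51 = 42.03 | 0.02 + 0.4998/40.5 = 0.03234 | 0.02 + 0.4998/42.03 = 0.03189 | 1.014 |
| r = 0.6, 4 outcome-only | 40.5 + 4 × 0.64 = 43.06 | 0.02 + 0.6272/40.5 = 0.03549 | 0.02 + 0.6272/43.06 = 0.03457 | 1.027 |

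The loss is 1.4 to 2.7% of the variance, or about 1% of the standard error (√1.014 = 1.007; √1.027 = 1.013).

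**Step 5. Power.** On the raw-point reading, counting every student without a baseline as lost and nothing else missing, t-based power goes from 81.0% to 80.0, 78.9, 77.6 and 76.3% at assumed absence of 5, 10, 15 and 20% (135, 270, 405 and 540 of 2,700 students). These figures overstate the loss, since some absentees would miss the post-test too and no covariate adjustment is allowed for. On the Cohen's d reading, power stays above 99.9% throughout.

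**Step 6. Could selection differ by arm?** Theoretical framework places staff workshops at the start of each wave. Parental meetings places information to families in intervention schools at the start of the school year or term. Data collection places baseline in autumn. Together these suggest that intervention schools may know their arm before the baseline visit. No sentence gives the order of allocation and baseline.

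**The case against.** The best defence is that the exclusion is inferred. The sentence says who will be included and does not use the word *only*, whereas the per-protocol sentence does. Baseline measurements is also a general term: earlier grades come from the schools and parental education from a register, so a student absent on the test day may still hold some baseline data. Catch-up visits are not ruled out, and a data analysis plan that is not shown was filed with the registration. All of this lowers certainty about how many students are affected. It does not remove the conflict, because the article states an inclusion rule next to an intention-to-treat claim and nothing readmits students who have only an outcome.

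A second defence is that a closed cohort fixed before the intervention is respectable, since it keeps out students who join or consent once allocation is known. That is a sound reason to exclude late joiners, and the fix must respect it. It is no reason to drop students already enrolled when baseline was taken.

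Three stronger readings are tempting and are not supported:

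- **That the comparison is biased.** If baseline precedes allocation, the restriction costs mainly precision and representativeness. The order is not stated, so bias is possible and not shown.
- **That the rule applies outcome by outcome**, so that a student without a valid baseline accelerometer week (the Students section requires "a minimum of 3 days, including at least one weekend day, will be considered a valid week") is lost from the activity analyses. The rule is not tied to any instrument, and imputation is not limited to post-intervention values. The ordinary reading keeps that student and imputes the gap.
- **That the trial becomes underpowered.** The absence rates are assumed, and the realistic loss is about 1% of the standard error.

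**Conclusion.** The point holds as a conflict between the stated inclusion rule and the stated principle, on the natural reading of the rule. Its size is modest: about 1.4 to 2.7% of the variance of the effect with baseline adjustment, and 4 to 5% at most without it. Both figures assume 10% absent at baseline, 90% retention, and 60 to 80% of absentees seen in spring; the lower range also assumes a correlation of 0.6 to 0.7. None of these rates is in the article. No documented figure changes. The stronger argument for acting is adherence to intention to treat, together with protection against attendance that differs by arm should allocation turn out to be known before baseline. This is a cheap improvement and does not threaten the trial.

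**What to change.** Replace the inclusion sentence with: *All students enrolled (consented) in randomised schools by the time of baseline measurement are analysed in the arm of their school; missing baseline and post-intervention values are imputed in the planned multiple imputation, with a model that respects clustering by school.* Add that students who join or consent later are not included, so that attendance at the post-test does not become a new route into the analysis. Report the baseline-present set as a sensitivity analysis, which fits the missing-data sensitivity analyses already promised.

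The cost is one sentence, slightly more imputation work because baseline values become targets, and reliance on missing at random for missing baselines. No new data are needed. If the sponsor already intends this analysis set, the wording still needs correcting to say so.

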### Control group

The control group will have unchanged school schedules and will be offered the intervention after the post-intervention measurements in the following school year.

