#### Fidelity and dose

Fidelity will be assessed through structured documentation by the teachers involved in delivering the intervention. Teachers will be asked to document all performed activities. For the physical activity sessions, the teachers will document the type and intensity of the activities. In addition, the teachers will document any adaptations made to the intervention protocol and the reasons for these adaptations. Implementation dose will be assessed as the dose delivered (the number of sessions) and the dose received (student participation), provided by teachers.

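### The per-protocol analysis selects on fidelity, which exists only in the intervention arm, so randomisation does not protect it and it cannot be run blinded as promised

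*Protocol article*

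**What the plan says.** The Data analysis section of the protocol article makes the main analysis a mixed-effects model with individual and school levels, "using post-intervention data and following the intention-to-treat approach". The crude model is described as "including group allocation as a predictor and adjusting for baseline values of the corresponding outcome"; a second model adds gender and parental education. The section then adds a per-protocol analysis, "including only those participants with high fidelity to the intervention components". The sentence after that reads: "All analyses will be performed blinded to group allocation". It makes no exception for the per-protocol analysis.

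Two other sections determine what fidelity can mean here. Under Fidelity and dose: "Fidelity will be assessed through structured documentation by the teachers involved in delivering the intervention". Also there: "Implementation dose will be assessed as the dose delivered (the number of sessions) and the dose received (student participation), provided by teachers". Under Control group: "The control group will have unchanged school schedules and will be offered the intervention after the post-intervention measurements in the following school year".

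**The concern.** A per-protocol set is normally defined by a rule that can be applied in both arms. This rule cannot be. Control schools run no sessions before the outcome is measured, so no control student has a fidelity or dose value. The intervention arm is filtered on something that happens after randomisation and the control arm is not.

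Students who take part well, and schools that deliver well, may differ from the rest in ways that also affect later anxiety. The planned covariates remove only the part of that difference which they explain. A per-protocol contrast could then depart from zero with no programme effect, and readers may take it as the effect of the programme when properly delivered.

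The second issue is internal consistency. Building the set requires knowing who has fidelity data, and that reveals the arm.

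**Working it through.** **Consistency check (no assumptions needed).**

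1. The selection variable comes from teachers delivering the programme (Fidelity and dose).
2. Controls keep their usual schedules until after the post-intervention measurements (Control group).
3. From 1 and 2, the variable has values in the intervention arm only.
4. The per-protocol set is built from that variable (Data analysis), so only the intervention arm shrinks. An analyst who holds coded groups and also the intention-to-treat set can see which group lost students. With 50% kept, the counts are 675 against 1,350. Coding the arms does not preserve blinding.

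**Size of the possible bias.** The document gives no figure for this analysis, so there is none to reproduce.

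Inputs from Sample size calculation, taken as given: 27 schools per arm, 50 students per school (27 × 50 = 1,350 per arm), intraclass correlation 0.02, two-sided α = 0.05.

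Assumptions, not in the document: true effect zero; all controls kept; proportion p of intervention students kept, those with the highest participation; correlation r = 0.1 or 0.2 between participation and lower anxiety after baseline adjustment.

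Formulas:
- Bias in baseline-adjusted SD units = r × φ(c)/p, where c is the normal cut-off that leaves p above it.
- Design effect = 1 + (m − 1) × 0.02. Controls: m = 50, giving 1.98. Intervention: m = 50p.
- SE = √[design effect/(1,350p) + 1.98/1,350].
- Rejection rate = P(|Z + bias/SE| > 1.96).

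Worked case, p = 0.5: φ(0)/0.5 = 0.798, so the bias is 0.080 (r = 0.1) or 0.160 (r = 0.2). SE = √(1.48/675 + 1.98/1,350) = 0.0605. The ratios are 1.32 and 2.64, and the rejection rates 26% and 75%.

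| Kept | φ(c)/p | Bias, r = 0.1 / 0.2 | SE | False-positive rate |
|---|---|---|---|---|
| 50% | 0.798 | 0.080 / 0.160 | 0.0605 | 26% / 75% |
| 70% | 0.497 | 0.050 / 0.099 | 0.0570 | 14% / 41% |
| 80% | 0.350 | 0.035 / 0.070 | 0.0558 | 10% / 24% |
| 90% | 0.195 | 0.019 / 0.039 | 0.0549 | 6.5% / 11% |

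**Selection of whole schools.** If half the intervention schools are kept and r acts at school level, the relevant SD is √0.02 = 0.141. Bias = r × 0.798 × 0.141 = 0.011 or 0.023. SE = √(1.98/675 + 1.98/1,350) = 0.0663. The false-positive rate is 5.3% or 6.3%.

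**Simulation check.** 1,000 null trials were run per setting, with a baseline–outcome correlation of 0.6 (assumed) and a t-test on school means. Bias is in total SD units and therefore smaller. With 50% kept it was 0.06 and 0.12, with false-positive rates of 22% and 62%. With 70% kept it was 0.04 and 0.08, with rates of 12% and 32%. With r = 0 the per-protocol rate was about 5%. The intention-to-treat rate was about 4–6% throughout.

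**The case against.** The strongest reply is that the analysis is supplementary. Intention-to-treat is the stated approach for primary and secondary outcomes, and nothing here touches it. Nor does the article say that the per-protocol result will be presented as the programme's true effect. Both points stand and limit the weight of the issue.

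Three stronger readings are tempting, and the document does not support them.

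- *Every control is dropped.* A literal application would do this, but no comparison would remain, so it is hardly the intention. The handling of controls and the fidelity threshold may be in the analysis plan filed with the registration; their absence from the article is no fault. A threshold would still not create a control-side fidelity value or reconcile the blinding sentence.
- *The result is biased towards the programme, with false positives of 26–75%.* That range needs half the students to be discarded and the selection to act between students. Intervention components and Parental meetings both describe the sessions as mandatory, so more may be kept. Delivery rests with teachers and with each school's own resources (Discussion), so much of the variation may lie between schools. Lower participation by more anxious students is plausible but undocumented, and baseline adjustment removes part of any such selection.
- *The bias can equal the whole effect the trial can detect.* This needs a detectable effect of about 0.155 SD, which the protocol does not state. Against its stated d = 0.35, a bias of 0.08–0.16 is 23–46%, in the least favourable case in the table.

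An instrumental-variable remedy also has weaknesses here, which the fix must acknowledge.

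**Conclusion.** The point holds as a matter of design and consistency. The planned subset is defined after randomisation by a variable that only one arm can have. The resulting contrast is observational, protected only by baseline outcome, gender and parental education. It cannot be carried out under the unqualified blinding promise in the same section. Neither conclusion depends on an assumed number.

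The size and direction of bias are unknown. Under the stated assumptions, taking the table and simulation together, false-positive rates are about 6–11% with 90% kept, 10–24% with 80% kept and 22–75% with 50% kept. They are near 5–6% if whole schools are selected at an intraclass correlation of 0.02. The consequence may be negligible or serious, and the document does not allow a choice between them. The plan should be corrected, but the primary conclusion of the trial is not at risk.

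**What to change.** 1. Replace the high-fidelity subset with a complier-average causal effect: a two-stage model with allocation as instrument, dose received (sessions attended, 0 in controls) as exposure, baseline outcome as covariate and school-clustered standard errors. In its simplest form this is the intention-to-treat difference divided by the mean dose received in the intervention arm. If allocation has no effect, the numerator is centred on zero, and selection among attenders does not create one. If the subset is kept, report it beside this estimate as exploratory and non-causal.

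2. Label the complier-average analysis exploratory and state its main assumption, that allocation affects the outcome only through sessions attended. Staff workshops, parental meetings, researcher visits and audiobook subscriptions are all part of the intervention arm's package and may violate it. State also that the dose effect is taken as linear.

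3. Limit the blinding statement to the intention-to-treat analyses, and lock these before fidelity and dose data are merged.

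The cost is a change of wording and one additional model on data already planned. The interval will be wider than that of the subset analysis. The estimate relies on the exclusion assumption and on complete student-level attendance records, although any student-level per-protocol set would need those records too.
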